### Randomization and Blinding

Following informed consent, the baseline assessment and confirmation of eligibility, participants will be randomly assigned to 1 of 2 treatment groups: reSET-O or PEAR-008. Randomization lists will be prepared by the study sponsor (Pear Therapeutics) prior to the start of the study. Randomization will be 1:1 and stratified by site and gender with a block size of 10. An electronic list of IDs, access codes, and credentials will be securely provided to the sites. There will be no blinding; this is an open-label study.

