### Study Population and Sample Size

The trial will include 130 adults aged 18 to 60 years with opioid use disorder who are already receiving buprenorphine treatment, with no criteria regarding gender identity, race, or ethnicity.

Inclusion criteria are having the ability to provide informed consent, age 18 to 60 years, having adequate English proficiency, being within the first 120 days of starting buprenorphine, receiving buprenorphine pharmacotherapy under the care of a licensed health care provider and being willing to provide the name of the provider or practice, being capable of using common software apps on a smartphone, and having access to an internet-enabled smartphone that meets minimal operating system requirements for the duration of the study. Exclusion criteria are having a history of reSET-O use, having participated in user-testing of PEAR-008 or any investigational drug trials within 30 days of trial enrollment, or currently receiving methadone or naltrexone pharmacotherapy.

The sample size and power were based on the primary engagement outcome, determined by frequency of interaction with the intervention, percentage of module completion, and approval ratings. A sample size of 130, α=.05, and power=0.80 will allow for detection of a moderate effect size (*d*=0.50).

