**Secondary**			
	To evaluate the impact of PEAR-008 compared to reSET-O on treatment retention	Time to dropout (last contact with a participant)	
	To evaluate the impact of PEAR-008 compared to reSET-O on abstinence from illicit opioids	Abstinence will be defined as abstinence on patient self-reports (via timeline followback) and the absence of nonbuprenorphine opioids on saliva drug screens. Abstinence (binary outcome: yes or no) will be determined 9 times, weekly during weeks 1-8 and at week 12.	
	To evaluate participants’ digital therapeutic use patterns of PEAR-008 compared to reSET-O	Session duration; number of lessons and chapters completed; number of completed self-report assessments; response to notifications	
	To evaluate the impact of PEAR-008 compared to reSET-O on change in psychiatric symptom severity between baseline and follow-up	Depression symptoms with Patient Health Questionnaire–8; Anxiety symptoms with Generalized Anxiety Disorder–7	
	To evaluate the impact of PEAR-008 compared to reSET-O on change in recovery capital and resilience between baseline and follow-up	Brief Assessment of Recovery Capital–10; Connor-Davidson Resilience Scale–10	
	To evaluate participant motivation and satisfaction over time with PEAR-008 compared to reSET-O	Participant surveys administered at baseline, week 4, week 8, and week 12; participant interview at follow-up	
	To evaluate a more global measure of engagement by combining data from secondary endpoints 3-6	A multivariate analysis of variance combining data from secondary endpoints 3-6	

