### Assessments

#### Demographics

Demographic information will be collected at the baseline session. Variables to be collected will include age at time of consent, sex assigned at birth, race and predominant self-reported ethnicity, level of education, marital status, employment status, occupation, and legal status.

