### Endpoints

#### Primary Endpoint Analysis

Engagement with PEAR-008 and reSET-O will be defined as the number of active sessions per week. A session is defined as a set of in-app events with the same session ID. An active session is any session that contains some active participation in the app such as navigating to a different screen, engaging with a learning module, or responding to a notification. This endpoint was selected to allow a 1:1 comparison of content delivery method (eg, brief chapters vs longer lessons). The number of active sessions per week will be evaluated with a repeated measures mixed model of the form: *Number of Sessions in a Week = Week + Treatment + Week × Treatment + Subject Error + Random Error*. To evaluate the impact of treatment, this repeated measures mixed model will be compared to another of the form: *Number of Sessions in a Week = Week + Subject Error + Random Error* with a likelihood ratio test. The likelihood ratio test will be evaluated using model fit to maximize the log-likelihood.

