#### Secondary Endpoint Analysis

Abstinence will be self-reported by patients via timeline followback and assessed as the absence of opioids (except buprenorphine) on saliva drug screens. Data on abstinence (binary yes and no) will be evaluated with the 9 possible saliva drug screens and urine drug screen and timeline followback data at weeks 1-8 and week 12. Differences between the treatment arms in abstinence will be assessed with a generalized estimating equation analysis using the binomial abstinence outcome as the dependent variable, assessment time, treatment, and the interaction between assessment time and treatment as fixed effects and subject as a random factor. This generalized estimating equation will be compared to a second generalized estimating equation without a treatment term using a likelihood ratio test to evaluate the impact of treatment. A treatment responder analysis will also be conducted, with a treatment responder defined as someone with ≥80% of all saliva drug screens and urine drug screens and timeline followback reports negative for all nonprescribed opioids over the course of the trial.

Treatment retention will be measured as time to dropout (number of days from baseline to last face to face contact) and analyzed using the Kaplan Meier method followed by a log rank test to compare treatment groups.

Patient assessments of recovery capital (Brief Assessment of Recovery Capital–10) resilience (Connor-Davidson Resilience Scale–10) and severity of co-occurring psychiatric symptoms (Patient Health Questionnaire–8 and Generalized Anxiety Disorder Questionnaire–7) will be evaluated with a repeated measures mixed model in a manner consistent with the primary endpoint.

Participants’ use patterns with PEAR-008 and reSET-O will include total time engaged, number of lessons and chapters completed, number of lessons and chapters repeated, number of completed self-report assessments, and response to notifications. Descriptive statistics of each treatment arm will be summarized and differences between PEAR-008 and reSET-O will be assessed with a *t* test (or its nonparametric alternative if the distributional assumptions are violated).

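### The stated models leave out the stratification factors, and the symptom and recovery scales borrow a model whose test does not isolate change from baseline

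*Protocol article*

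**What the plan says.** Randomization and Blinding: "Randomization will be 1:1 and stratified by site and gender with a block size of 10".

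Primary Endpoint Analysis gives the full model as "Number of Sessions in a Week = Week + Treatment + Week × Treatment + Subject Error + Random Error" and compares it, by a likelihood ratio test, with "Number of Sessions in a Week = Week + Subject Error + Random Error". Neither line has site or gender.

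Secondary Endpoint Analysis lists the terms of the abstinence GEE: assessment time, treatment, their interaction, and subject. Retention is compared by Kaplan-Meier and a log-rank test, with no strata stated. Exploratory Endpoint Analysis carries the GEE form over to medication adherence and the mixed-model form over to the CBT skills scale.

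Table 1 words the psychiatric objective as "To evaluate the impact of PEAR-008 compared to reSET-O on change in psychiatric symptom severity between baseline and follow-up", and the objective for recovery capital and resilience is worded in the same way. The four scales (PHQ-8, GAD-7, BARC-10, CD-RISC-10) are measured at baseline and weeks 4, 8 and 12. Their analysis is given in one clause: they "will be evaluated with a repeated measures mixed model in a manner consistent with the primary endpoint".

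**The concern.** Two features of the design do not reach the analysis.

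**Stratifiers.** Stratified allocation forces the arms to be alike on site and gender, which lowers the true variance of the treatment difference if those factors predict outcome. A model without them leaves their variance in the residual, so its standard error is too large and part of the gain from stratifying is given away.

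**Baseline.** The primary outcome, active sessions per week, has no pre-treatment value, so its model has no place for one. The scales do have a baseline, and change from it is their objective. Copying the primary form leaves two readings. Either baseline is one level of Week, or only the follow-up visits are modelled and baseline goes unused. On the first reading the test mixes in a difference that treatment cannot have caused; on the second it discards the best available predictor of the outcome.

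**Working it through.** **1. The plan's own figure.** The article states: "A sample size of 130, α=.05, and power=0.80 will allow for detection of a moderate effect size" of d = 0.50. With 65 per arm and two-sided alpha 0.05 (sidedness is not stated), the standardised difference is 0.50 × √(65/2) = 2.850, and power is Φ(2.850 − 1.960) = 0.813. The t-based requirement for power 0.80 is 64 per arm, 128 in all. N = 130 is therefore reproduced as an unadjusted two-group comparison.

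**2. Leaving out site and gender.** The article does not say how much variance they explain, so R² is assumed. Take each participant's mean session count, with strata balanced by design. The true variance of the treatment difference is then (1 − R²) × 2σ²/65, while the unadjusted model estimates about 2σ²/65.

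- Unadjusted type I error: 2 × [1 − Φ(1.960/√(1 − R²))]
- Unadjusted power: Φ((2.850 − 1.960)/√(1 − R²))
- Adjusted power: Φ(2.850/√(1 − R²) − 1.960)

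| R² | Type I error, unadjusted | Power, unadjusted | Power, adjusted |
|---|---|---|---|
| 0.05 | 0.044 | 0.820 | 0.833 |
| 0.10 | 0.039 | 0.826 | 0.852 |
| 0.20 | 0.028 | 0.840 | 0.890 |
| 0.30 | 0.019 | 0.856 | 0.926 |

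A simulation of 20,000 trials per scenario (four strata, permuted blocks of 10, N = 130) agrees. At R² = 0.10, type I error was 0.037 without the factors and 0.050 with them, and power was 0.82 against 0.85. At R² = 0.30, type I error without the factors was 0.020, and power was 0.85 against 0.92.

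**3. The scales.** Assume equal correlation ρ = 0.6 between all four visits, a constant effect of 0.3 SD at weeks 4, 8 and 12, Week as a categorical factor, 65 per arm and no missing data.

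- The variance of the three-visit follow-up mean is (1 + 2ρ)/3 = 0.733. After adjustment for baseline it is 0.733 − 0.6² = 0.373.
- The noncentrality is 0.3² × 32.5/0.733 = 3.99 without baseline and 0.3² × 32.5/0.373 = 7.83 with it.
- With a constant effect and equal correlations, the joint tests have the same noncentralities as the 1-df tests. The chi-square critical values are 3.84 (1 df), 7.81 (3 df) and 9.49 (4 df).

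| Analysis | Noncentrality | Power, joint test | Power, 1 df |
|---|---|---|---|
| Weeks 4, 8, 12, baseline unused | 3.99 | 0.36 (3 df) | 0.51 |
| Weeks 4, 8, 12, baseline-adjusted | 7.83 | 0.64 (3 df) | 0.80 |
| Baseline as a level of Week, test as specified | 7.83 | 0.59 (4 df) | n/a |

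The 1-df gain from adjustment depends on ρ: 0.65 to 0.73 at ρ = 0.3, and 0.48 to 0.87 at ρ = 0.7.

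**4. What the 4-df test measures.** Going from the full to the reduced model drops Treatment and Week × Treatment together. With baseline among the four levels of Week that is 1 + 3 = 4 df, one of which belongs to the baseline difference. Suppose a chance gap of 0.35 SD is carried unchanged through all four visits, so the arms do not differ in change at all. Its contribution to the chi-square is 0.35² × 32.5 × 4/(1 + 3ρ), which is 8.4, 6.4 and 5.1 at ρ = 0.3, 0.5 and 0.7, against the critical value of 9.49.

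**The case against.** **Leaving out the strata does little harm.** This stands. In the linear model it causes neither bias nor inflated type I error, and N = 130 remains adequate. A reader might set 0.81, the power when strata explain nothing, against 0.83-0.85. That overstates the gain, because stratified allocation also helps the unadjusted test. The right comparator is 0.820-0.826, so at R² of 5-10% the gain is 1 to 3 points. The article gives no figure showing that site or gender predicts session counts.

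**The scales may not be unadjusted at all.** A reader might infer that baseline is ignored. The article does not say so. Baseline is one of the four assessment times, and treating it as a level of Week is a natural reading, in which Week × Treatment carries the change. On that reading little power is lost: 0.59 against 0.64 for the adjusted joint test. Most of the distance from 0.59 to 0.80 comes from moving to a 1-df contrast, not from using baseline. What stands is that the stated test does not isolate change.

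**Chance imbalance does not produce excess false positives.** This also stands. Over repeated randomisation with no effect, the joint test keeps its nominal size. The 0.35 SD example shows what a given rejection could mean, not a raised error rate.

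**Detail may sit in an SAP.** For wholly unstated matters that would be an answer. Here the article writes out both primary models and lists the GEE terms, and applies the primary form to the scales. The point concerns what those stated models contain.

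**Gender and sex.** The demographics name "age at time of consent, sex assigned at birth, race and predominant self-reported ethnicity", and a reader might conclude that the stratifier is not collected. That does not follow: the list need not be exhaustive, and gender is needed to assign from the stratified randomisation lists.

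**Conclusion.** The point holds as a moderate improvement to stated models, not as a threat to validity.

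On the stratifiers, the mismatch between design and analysis is plain in the text. Its cost is a conservative primary test: type I error about 0.044-0.039, and power about 0.82-0.83 instead of 0.83-0.85, if site and gender explain 5-10% of variance. The loss grows if they explain more and vanishes if they explain nothing. These figures are for the simple two-group comparison behind the sample size.

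On the scales, the stated analysis does not match the objective on either reading. With baseline as a level of Week the fault is interpretive: the 4-df test has the right size but includes the baseline difference. With baseline left out the fault is lost precision, 0.36 against 0.64 (3 df) or 0.51 against 0.80 (1 df), under an assumed correlation of 0.6 and a constant 0.3 SD effect.

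**What to change.** - **Mixed models:** add site and gender, as used at randomisation, as fixed effects in both the full and the reduced model, so that the likelihood ratio test still concerns treatment alone.
- **GEEs (abstinence, medication adherence):** add the same two factors, and note that the odds ratio then becomes conditional on them.
- **Retention:** stratify the log-rank test by site and gender, merging sparse strata.
- **PHQ-8, GAD-7, BARC-10, CD-RISC-10 and the CBT skills scale:** model weeks 4, 8 and 12 with the baseline score as a covariate, or keep baseline as an outcome and constrain the arms to a common baseline mean. Test the treatment effect on follow-up only, and name the contrast (for example week 12, or the follow-up average).

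The cost is model wording and a little analysis work. The scales are already measured at baseline and the stratifiers come from the randomisation list, so no new data are needed. The wording should be settled before the data are analysed.

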### Study Interventions

#### reSET-O

reSET-O is a prescription digital therapeutic for opioid use disorder delivered concurrently with standard buprenorphine treatment [13]. reSET-O delivers therapy in the form of a series of 67 interactive lessons via a patient-facing mobile software app. A typical therapy lesson comprises a behavioral therapy component and skill-building exercises. The therapeutic content is based on the community reinforcement approach, an intensive addiction-specific form of cognitive behavioral therapy that has been validated for opioid use disorder [14]. Therapy lesson content is delivered primarily via written text but may include videos, animations, and graphics. After most therapy lessons, the user undergoes fluency training, which is a method of questioning that has been demonstrated to promote learning and improve both short-term and long-term retention of material [27].

reSET-O also includes contingency management delivered via a virtual rewards wheel. Contingency management rewards are either virtual (thumbs up icon) or tangible rewards (gift card with value range US $5 to $100) that can be earned for completion of therapy lessons. Studies [28] have consistently demonstrated that contingency management interventions, particularly abstinence-based incentives, can support treatment and recovery in individuals with a wide range of substance use disorders. The odds of winning a tangible reward are 50% each time a reward is possible (wheel spin or mystery box), with higher-value rewards occurring less often. The odds of receiving a $100 gift card are 0.2%, whereas the odds of receiving a $5 gift card are 41.8%. The value of the rewards is commensurate with the amount of time users typically spend with the prescription digital therapeutic over the 12 weeks of treatment. Users are also prompted to report substance use, cravings, and triggers every 72 hours. A user can self-initiate reports of substance use, cravings, and triggers at any time. reSET-O contains an optional daily medication reminder that can be set to enhance adherence to buprenorphine for opioid use disorder.

#### PEAR-008

PEAR-008 is an investigational device with therapeutic content and a contingency management reward system that are similar to those in reSET-O; however, clinical content enhancements have been made, and the therapy has been reformatted as a game with mechanics designed to promote engagement. Content enhancements include use of person-centered language and lowering the reading level to make it more accessible. In PEAR-008, the reSET-O therapy lessons were divided into a tiered structure of shorter chapters with the intent of providing small, achievable goals to help keep users motivated and engaged. Each chapter has an associated quiz based on the fluency training approach.

The PEAR-008 home screen shows a nature scene that transitions from winter to summer as the patient progresses through therapy (Figure 1). The game economy of PEAR-008 is variable, consisting of the ability to earn stars that unlock virtual rewards such as birds and home-screen upgrades, as well as Mystery Boxes. The Mystery Boxes replace the contingency management rewards wheel in reSET-O and contain either virtual (stars) or tangible rewards (gift card with value ranges from $5 to $100) with the same odds of winning a tangible reward at each level of value as those in reSET-O. Similar to reSET-O users, PEAR-008 users earn the opportunity for contingency management rewards by completing fluency training quizzes (ie, therapy lessons). Engagement is also incentivized: a user can earn rewards by repeating a chapter and by engaging at least once daily with PEAR-008. The user is required to complete a daily check-in the first time they open the app each day. The check-in consists of a series of questions related to substance use, medication use, general recovery status, and recovery-specific questions regarding cravings, triggers, and problems the user is managing.

**Figure 1 figure1:**
[figure not shown]
Screenshots from reSET-O (A) home screen and (B) contingency management rewards wheel screen, and PEAR-008 (C) home screen with winter scene, (D) contingency management rewards mystery box screen, and (E) home screen with summer scene. Content is accessed via the icons on the windowsill, lessons are represented by the stack of books icon, worksheets are represented by paper and pencil, and rewards are represented by the treasure box.

### Study Procedures

#### Overview

All study visits will be conducted remotely. Each prospective participant will complete a short screening assessment, and if basic eligibility is confirmed, complete informed consent procedures and sign an electronic informed consent form prior to completing the baseline assessment. After baseline assessments, participants will be randomly assigned to either reSET-O or PEAR-008 groups. Study staff will assist each participant with installation of their assigned digital therapeutic on their mobile device. Staff will provide training on the app’s use. Study participants will be enrolled for 12 weeks, with weekly virtual sessions during weeks 1-8 and a final visit at week 12, to evaluate the impact of reSET-O and PEAR-008 on participant engagement and treatment outcomes. Participants will also complete slightly longer assessments at weeks 4 and 8.

Weekly study assessments completed during the first 8 weeks of treatment include saliva drug screening (participants will receive drug screening equipment on a regular basis by mail; urine drug screen results may be retrieved from the electronic medical record for AREF participants), timeline followback [29], and adverse event reporting. Additional self-report assessments will be delivered at week 4 and week 8.

Participants will attend a virtual end of treatment study session at 12 weeks to complete the following: saliva drug screening, timeline followback, and adverse event reporting assessment. Additional measures will be assessed at the 12-week follow-up visit (Table 1).

**Table 1 table1:** Study objectives and endpoints.

Objective			Endpoint
**Primary**			
	To evaluate participant engagement with PEAR-008 compared to that with reSET-O. The hypothesis is that PEAR-008 group will have significantly greater participant engagement than the reSET-O group.	Number of active sessions with PEAR-008 or reSET-O per week	
**Secondary**			
	To evaluate the impact of PEAR-008 compared to reSET-O on treatment retention	Time to dropout (last contact with a participant)	
	To evaluate the impact of PEAR-008 compared to reSET-O on abstinence from illicit opioids	Abstinence will be defined as abstinence on patient self-reports (via timeline followback) and the absence of nonbuprenorphine opioids on saliva drug screens. Abstinence (binary outcome: yes or no) will be determined 9 times, weekly during weeks 1-8 and at week 12.	
	To evaluate participants’ digital therapeutic use patterns of PEAR-008 compared to reSET-O	Session duration; number of lessons and chapters completed; number of completed self-report assessments; response to notifications	
	To evaluate the impact of PEAR-008 compared to reSET-O on change in psychiatric symptom severity between baseline and follow-up	Depression symptoms with Patient Health Questionnaire–8; Anxiety symptoms with Generalized Anxiety Disorder–7	
	To evaluate the impact of PEAR-008 compared to reSET-O on change in recovery capital and resilience between baseline and follow-up	Brief Assessment of Recovery Capital–10; Connor-Davidson Resilience Scale–10	
	To evaluate participant motivation and satisfaction over time with PEAR-008 compared to reSET-O	Participant surveys administered at baseline, week 4, week 8, and week 12; participant interview at follow-up	
	To evaluate a more global measure of engagement by combining data from secondary endpoints 3-6	A multivariate analysis of variance combining data from secondary endpoints 3-6	
